### Sample size calculation and statistical analysis

The calculation of sample size was based on the primary outcome of change in NIH-CPSI total score from baseline to the 8^th^ week of treatment (mean of 8 weeks of data). According to previous literature [12], after 10 weeks of sham acupuncture treatment, NIH-CPSI scores decreased by 6.2, with a standard deviation of 10.3. We estimated that for a 13.3-point difference in the NIH-CPSI score with a standard deviation of 4.5, and based on our clinical experience and data from previous research, the decrease in the NIH-CPSI total score should be more than 6 points (i.e., the minimal clinically important difference, MCID) [28]. Therefore, we will need to recruit 34 patients per group from Guang’anmen Hospital of Chinese Academy of Chinese Medical Sciences and Yantai Hospital of Traditional Chinese Medicine to obtain 90 % power and a significance level of 5 % while allowing for a 20 % dropout rate.

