The data will be analysed using SPSS software Ver.19.0 (IBM SPSS Statistics, IBM Corp, Somers, New York), and the data analysis will be based on the intention-to-treat (ITT) principle regarding baseline characteristics. If there are significantly more dropouts in the control group than in the treatment group, we will conduct a secondary analysis of subjects who have completed the treatment according to the protocol. The outcomes for evaluating changes between the groups will be based on the outcome of the NIH-CPSI at different time points. The significance levels will be two-sided and reported at a 5 % level. For continuous measurement data, the mean, standard deviation, median and interquartile range will be represented. If the data are normally distributed, analysis of covariance will be used because the centres and baseline variables in this study are covariates that are not manipulated by the researchers but may still have an effect on the efficacy of acupuncture. If the distribution is not normal, we will use generalized estimating equations, if needed, to account for the cumulative acupuncture frequency and to observe whether increasing treatment sessions results in increased efficacy for patients. Linear regression will be used to explore whether the patients’ expectations have an impact on treatment. For categorical data, a CMH (Cochran-Mantel-Haenszel) test will be used, and the data will be represented as case and percentages. Missing data will be assumed to be missing randomly and will be imputed using multiple imputation.

Table 2 summarizes the details of the analysis methods for the primary and secondary outcomes.

**Table 2 Tab2:** Analysis methods for outcomes

Outcomes	Time frame	Statistics
Primary outcome		
NIH-CPSI total score and change from baseline	baseline, week 1-8	Covariance analysis or generalized estimating equations
Secondary outcomes		
NIH-CPSI subscales score	Baseline, week 4,8,20,32	Covariance analysis or generalized estimating equations
NIH-CPSI total score in follow-up	week 20,32	Covariance analysis or generalized estimating equations
IPSS total score and change from baseline	baseline, week 4,8,20,32	Covariance analysis or generalized estimating equations
Global response assessment improvement	week 4,8,20,32	CMH test or nonparametric test
Degree of expectation	baseline	linear regress
Degree of satisfaction	week 8,20,32	CMH test or nonparametric test

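### A normality check on the outcome data chooses between ANCOVA and GEE for the primary analysis; the trigger is unsound, and the GEE branch is tied to a different, undefined question about session counts

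*Protocol article*

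**What the plan says.** The rule is in the Protocol article, section Sample size calculation and statistical analysis. For continuous measurements, "If the data are normally distributed, analysis of covariance will be used", with centre and baseline variables as covariates. For the other case: "If the distribution is not normal, we will use generalized estimating equations, if needed, to account for the cumulative acupuncture frequency". The same sentence adds a second purpose for the GEE, to see whether efficacy rises with the number of sessions.

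Table 2 gives the method for the primary outcome as "Covariance analysis or generalized estimating equations". It repeats that entry for the NIH-CPSI subscales, the NIH-CPSI total at follow-up and the IPSS.

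The same section bases the sample size on the between-group difference in change in NIH-CPSI total score, taken as the mean over the 8 treatment weeks. On error control it says: "The significance levels will be two-sided and reported at a 5 % level".

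**The concern.** Four things are wrong with the rule as written.

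- **No single primary analysis is named.** The text does not say whether raw values or residuals are checked, whether arms are pooled, or by what test. The words about need add discretion: if the data are not normal and GEE is judged unnecessary, no method is named.
- **The trigger is not the right one.** ANCOVA relies on well-behaved residuals and a moderate sample, not on a normally distributed outcome.
- **The alternative does not answer the trigger.** GEE deals with correlated repeated measures. It does not assume normality, but its inference rests on a large-sample argument, as ANCOVA's does when data are not normal.
- **The GEE branch carries another question.** Accounting for accumulated sessions is dose-response. The trial is powered for a randomised difference between arms.

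At stake are the single confirmatory p-value and, on some readings of the session clause, what the reported effect means.

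**Working it through.** **1. The plan's own figure.** Inputs from the sample size paragraph: "NIH-CPSI scores decreased by 6.2, with a standard deviation of 10.3" (sham); "13.3-point difference in the NIH-CPSI score with a standard deviation of 4.5"; "90 % power and a significance level of 5 % while allowing for a 20 % dropout rate". The sample size reproduces only if 13.3 is read as the decrease in the acupuncture arm, although the text calls it a difference.

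- Difference = 13.3 − 6.2 = 7.1
- n = (10.3² + 4.5²)(1.960 + 1.282)² / 7.1² = 126.34 × 10.507 / 50.41 = 26.3, so 27 per arm
- 27 / 0.8 = 33.75, so 34 per arm, as stated

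The same reading is used below.

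**2. Does GEE give something ANCOVA does not?** Take complete data at all 8 weeks, covariates constant within a patient, and exchangeable working correlation. The GEE treatment coefficient then equals the ANCOVA coefficient on each patient's 8-week mean. Only the standard error and reference distribution differ.

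**3. How often would the check fire when each arm is exactly normal?** Shapiro-Wilk at 5 % is assumed, because the protocol names no test. Arms are N(13.3, 4.5²) and N(6.2, 10.3²).

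| What is checked | 34 per arm | 27 per arm |
|---|---|---|
| Values pooled across arms | 68 % | 58 % |
| Residuals from arm means | 35 % | 28 % |
| Each arm separately, either rejects | 10 % | 10 % |
| Pooled, equal SDs of 7.95, same 7.1 difference | 5 % | 5 % |

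The third row is what two 5 % checks should give: 1 − 0.95² = 9.75 %. A fuller model with weekly values, baseline and centre gives 59 % and 49 % for the pooled check. The last row shows that the unequal planning SDs drive the result.

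**4. Type I error.** There were 20,000 null trials per scenario, with 8 weekly values and with baseline and centre as covariates. Assumptions not in the protocol: within-patient correlation 0.7, baseline SD 6, uncorrected sandwich variance with a Wald z test, and Shapiro-Wilk on pooled values as the switch. Simulation error is about 0.15 points. Each cell shows 34 per arm / 27 per arm.

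| Errors, SDs | ANCOVA | GEE always | Two-stage rule |
|---|---|---|---|
| Normal, equal | 5.2 / 5.0 % | 6.3 / 6.5 % | 5.2 / 5.0 % |
| Normal, 10.3 and 4.5 | 5.0 / 5.0 % | 6.1 / 6.5 % | 5.3 / 5.4 % |
| Exponential, equal | 4.7 / 4.8 % | 5.8 / 6.4 % | 5.7 / 6.2 % |
| Log-normal, equal | 4.2 / 4.1 % | 5.3 / 5.6 % | 5.3 / 5.5 % |
| Exponential, 10.3 and 4.5 | 6.4 / 6.2 % | 7.7 / 7.7 % | 7.4 / 7.2 % |
| Log-normal, 10.3 and 4.5 | 7.2 / 7.5 % | 8.6 / 9.2 % | 8.3 / 8.7 % |

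A hand check supports the first row. With 4 coefficients the average leverage is 4/68 = 0.059 or 4/54 = 0.074, so the uncorrected standard error is too small by about √(1 − 0.059) = 0.970 or √(1 − 0.074) = 0.962. The cut-off 1.96 then acts like 1.90 on 64 degrees of freedom (6.2 %) or 1.89 on 50 (6.5 %).

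A fitted exchangeable GEE gave 6.4 % and 7.2 % (1,000 trials each, error about 0.8 points). A separate 6,000-run simulation gave 6.3 to 7.5 % with normal errors. A leverage-corrected variance with a t reference returns 5.2 % and 5.0 % in the normal, equal-SD case.

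**5. What does the session clause mean?** Treatment is scheduled three times weekly for 24 sessions, so the scheduled cumulative count is 3 × week.

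- If scheduled sessions are meant, the variable is time under another name. Randomisation is intact, but with a time interaction the coefficient reported may not be the powered contrast.
- If attended sessions are meant, the model conditions on something that happens after randomisation. The Discussion section itself expects a fairly high dropout rate in the control group, so attendance could differ by arm.

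The protocol does not say which.

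**The case against.** The strongest defence has four parts.

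- **Variance estimator.** The excess in GEE's type I error needs an uncorrected sandwich variance. The protocol names no estimator, and that detail commonly sits in an analysis plan, which is not shown here. This stands: a reader might infer that the GEE branch must exceed 5 %, and the document does not support that.
- **Fair comparison.** With skew and the planning SDs, ANCOVA also exceeds 5 % (6.2 to 7.5 %). Most of the excess there comes from the data, not from GEE. This stands.
- **Trigger rate.** The 68 % figure holds only for values pooled across arms and depends on the unequal SDs. A reader might infer that the switch is likely even when nothing is wrong, but the check is undefined and the rate falls to about 10 % arm by arm. This stands.
- **Estimand and bias.** A reader might infer that the switch necessarily changes the estimand, or that adjusting for sessions biases the effect. Neither follows from the text. With complete balanced data the coefficient is the same, and harm arises only if attended sessions or a time interaction enter the efficacy model.

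It is also true that GEE does not assume normality, so turning to it is not illogical. It simply gains nothing here. None of this supplies a fixed primary method. An unseen analysis plan is no answer either, because the article states a rule and the rule itself is faulty.

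**Conclusion.** The concern holds as a defect of pre-specification. The primary analysis, and that of the secondary continuous outcomes, is left to an undefined normality check and a discretionary clause, and nothing elsewhere in the protocol fixes one method. This conclusion needs no simulation.

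The numerical cost is modest. GEE with an uncorrected sandwich variance runs at about 6 to 7 % with normal errors (7.5 % in one smaller run) and about 7 to 9 % with skew plus the planning SDs, roughly 1 to 2 points above ANCOVA. The rule as a whole stays near 5 to 6 % with normal data and reaches about 5 to 9 % with skewed data. These figures rest on the assumptions listed with the simulations and on reading 13.3 and 6.2 as arm decreases.

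The session clause is ambiguous, and bias from it is not demonstrated. On either reading it asks a question other than the one powered.

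**What to change.** - Name ANCOVA of the 8-week mean change in NIH-CPSI total score, adjusted for baseline NIH-CPSI and centre, as the single primary analysis whatever the distribution. Use the matching ANCOVA for the secondary continuous outcomes.
- Delete the normality trigger and the discretionary wording, and replace the either/or entries in Table 2.
- Add a sensitivity analysis: heteroscedasticity-robust (for example HC3) standard errors, since the planning SDs differ, or a rank-based or permutation analysis. HC3 lessens the problem but does not remove it. In one skewed scenario with unequal SDs and 27 per arm it gave 6.3 %, against 7.1 % for ordinary ANCOVA and 8.6 % for uncorrected GEE.
- Move the session question to a model labelled exploratory. State whether sessions are scheduled or attended, use a small-sample-corrected variance if it is a GEE, and keep session count out of the efficacy models.

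The cost is wording and a little extra analysis. No new data are needed, and the sample size stays at 34 per group. The change should be made before unblinding.

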**Methods:**

This study is designed as a randomized, sham acupuncture-controlled trial. We will compare patients with CP/CPPS in an acupuncture group and a sham acupuncture group. Sixty-eight patients will be randomly allocated to receive acupuncture or sham acupuncture. The treatments will consist of 30-min sessions, three times weekly, for 8 weeks. The primary outcome measure is change in the weekly mean National Institutes of Health Chronic Prostatitis Symptom Index (NIH-CPSI) total score from baseline through the 8-week treatment period. Secondary measures include the NIH-CPSI subscale scores, the total International Prostate Symptom Score (IPSS), patients’ response rate, and patient satisfaction after treatment. We will also assess changes in the NIH-CPSI total score from baseline at the 20^th^ and 32^nd^ week of follow-up.

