### Recruitment procedures

We will recruit the participants using advertisements in newspapers, on television, and on the Internet. Prospective participants will obtain a good understanding of the trial by reading the advertisement, which will include a brief introduction of the population needed, the contact information of the researchers, and details of the acupuncture intervention and of the comparison (all participants will be informed that there are two acupuncture groups, i.e., a traditional acupuncture group and a sham acupuncture group, in which blunt needles are used to stimulate the acupoint skin, and that they have a 50 % chance of being allocated into either of the two groups). If the patient is eligible and interested in the trial, they will be invited to consult with the study doctors; after the doctors have provided a diagnosis, the patients will be recruited. All of the participants will be required to sign an informed consent form before the trial that will include an introduction of CP/CPPS, the inclusion and exclusion criteria of the trial, and an introduction to the interventions. In addition, participants have the right to withdraw from the trial at any time.

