### Interventions and comparison

#### Treatment group

According to records in the ancient Traditional Chinese Medicine work *Huangdi Neijing*, acupuncture points belonging to bladder meridian (BL) have a noticeable effect on urinary disease. Furthermore, spleen meridian (SP), kidney meridian (KI), and liver meridian (LR) intersect at Sanyinjiao (SP 6), one of the most frequently used acupuncture points for urogenital disease [19, 20]. In addition, the treatment was based on the theory of neuroanatomy [10, 21, 22] and consensus among acupuncture experts in Guang’anmen Hospital. Therefore, we chose the following acupuncture points: Zhongliao (BL 33), Shenshu (BL 23), Huiyang (BL 35), and Sanyinjiao (SP 6) (Table 1). After the patients are relaxed and in a prone position, acupuncturists will use 75 % alcohol pads to sterilize the skin around the acupuncture points and then insert steel needles (Huatuo, Suzhou, China 0.3 mm*40 mm/0.3 mm*75 mm) into the acupuncture points. For bilateral Zhongliao (BL 33), the needle will be inserted approximately 50–60 mm with a 45-degree angle. For Huiyang (BL 35), the needle will be inserted approximately 50–60 mm. For Shenshu (BL 23) and Sanyinjiao (SP 6), the needles will be inserted vertically to a depth of 25–30 mm. Acupuncturists will twirl at BL23, BL35 and SP 6 to achieve and enhance the sensation of aches, heaviness or numbness in the area surrounding the inserted needle (known as de qi), and the manipulations will be performed a total of three times during 1 session (every 10 min). For bilateral BL 33, which are located in the 3^rd^ posterior sacral foramina, needles will be inserted without lifting or rotating based on the characteristics of the points. There are 24 treatment sessions after baseline that occur three times a week, and the participants will receive a 30-min treatment each session.

**Table 1 Tab1:** Measurements at different time points

Measurements	baseline	1 week	2 weeks	3 weeks	4 weeks	5 weeks	6 weeks	7 weeks	8 weeks	20 weeks	32 weeks
NIH-CPSI total score	**×**	**×**	**×**	**×**	**×**	**×**	**×**	**×**	**×**	**×**	**×**
NIH-CPSI subscales score	**×**				**×**				**×**	**×**	**×**
IPSS total score	**×**				**×**				**×**	**×**	**×**
Global response assessment	**×**				**×**				**×**	**×**	**×**
Degree of expectation	**×**										
Satisfation									**×**	**×**	**×**

*NIH-CPSI* The National Institutes of Health Chronic Prostatitis Symptom Index, *IPSS* International Prostate Symptom Score

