#### Control group

The control group will receive sham acupuncture at the same acupuncture points as the treatment group. The sham needle with a blunt tip used in the control group is similar to the Streitberger needle (Fig. 2 provides a diagram to illustrate the sham acupuncture applied in this trial) [23]. Acupuncturists will gently lift, thrust, and twist the sham needles to simulate the treatment procedure, thus blinding the patients to the intervention. Each acupuncture point will undergo the same twirling motion as the acupuncture group. The duration and frequency of the sessions will be the same as in the acupuncture group. To ensure blinding, the investigators will make appointments with each participant on alternate days to prevent crosstalk between groups. To test the success of the blinding, the participants will be asked to answer the following question after the 4^th^ week treatment: “Do you think you received traditional acupuncture (A) or sham acupuncture (blunt needles used to stimulate the acupoint skin) (B)?” The participants can answer “A”, “B” or “unclear” (these two interventions will be demonstrated before the treatment, and all participants will have a good understanding of both interventions). Any medication usage should be recorded, including the name of the medicine, the dosage and the session. We will compare the proportion of subjects using medicine and the mean days of medication use between the groups.

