### Outcome measures

#### Primary outcome measures

The primary outcome of this study is the change in the NIH-CPSI total score, which will be measured from baseline to the 8^th^ week. After we have collected data for 8 weeks, the average score from each week will be calculated.

The NIH-CPSI is a validated, self-reported questionnaire that is widely used to assess CP/CPPS patients [24, 25]. It contains 13 items that are scored in three discrete domains: pain, urinary symptoms and impact on quality of life. A score of 0 indicates that the condition described in the question never occurs.

The secondary outcome measures include the following (for the first three secondary outcomes, we will measure the change from baseline):NIH-CPSI total score at the 20^th^ and 32^nd^ week.NIH-CPSI subscale scores at the 4^th^, 8^th^, 20^th^, and 32^nd^ week.IPSS total score at the 4^th^, 8^th^, 20^th^, and 32^nd^ week. The International Prostate Symptom Score (IPSS) is another valid, reliable and sensitive measure for patients with lower urinary tract symptoms (LUTS). The IPSS has been translated into several languages, including Chinese, and it is widely used in clinical practice and research to determine the severity of LUTS, including incomplete bladder emptying, frequency of urination, intermittency, urgency, weak urine stream, straining and nocturia [26, 27]. Each of the questions is rated from 0 (not at all) to 5 (almost always), and according to the total symptom score, the severity of LUTS can be graded as mild (0–7), moderate (8–19) or severe (20–35).Global response assessment at the 4^th^, 8^th^, 20^th^, and 32^nd^ week. Patients who have at least a 50 % decrease compared to baseline in total NIH-CPSI score will be considered “responders”. We will compare the response rate between the two groups.Expectations that acupuncture might help CP/CPPS at baseline. This scale includes four brief questions to investigate whether patients are confident that acupuncture treatment will help their CP/CPPS.The degree of satisfaction for patients undergoing acupuncture treatment will be measured at the 8^th^, 20^th^, and 32^nd^ week.

Table 1 shows the time to visit and the data collection measurements at different time points.

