In this trial, we aim to clarify the efficacy and safety of acupuncture for treating CP/CPPS. We will calculate the mean NIH-CPSI scores over 8 weeks, and these scores will indicate the weekly efficacy of acupuncture during the 8 weeks of treatment; additionally, the mean value may provide more sufficient evidence for determining whether acupuncture is efficacious for treating CPPS. Furthermore, we will add an expectations scale to explore whether the patients’ expectations have a potential impact on the outcomes of acupuncture treatment. Nevertheless, this study has several limitations, including the small sample size and the unblinded acupuncturists. Due to the use of a sham acupuncture control, a relatively high rate of dropouts might be observed in the control group. Additionally, there is a risk that the blinding method may be unsuccessful in control participants, as the blunt tip needle will not leave puncture holes. Finally, a few participants might be recruited mistakenly due to the overlapping symptoms of CP/CPPS and BPH [41]. Nonetheless, the outcome assessors and patients will be blinded to decrease the potential for bias [42]. We hope that the results of this trial can provide both an evidence-based treatment option for patients suffering from CP/CPPS and an enhanced level of evidence on which to base guideline recommendations.

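### The planned look at whether more sessions give more efficacy cannot separate session number from elapsed time, because both arms follow one fixed schedule

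*Protocol article*

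**What the plan says.** In *Sample size calculation and statistical analysis*, the protocol article says that if the distribution is not normal, GEE will be used where needed to allow for cumulative acupuncture frequency and "to observe whether increasing treatment sessions results in increased efficacy for patients". The sentence does not list model terms and does not say where variation in session number would come from.

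The regimen is fixed elsewhere:

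- Abstract, *Methods*: "The treatments will consist of 30-min sessions, three times weekly, for 8 weeks".
- *Treatment group*: "There are 24 treatment sessions after baseline that occur three times a week".
- *Control group*: "The duration and frequency of the sessions will be the same as in the acupuncture group".
- *Recruitment procedures*: patients are told that "they have a 50 % chance of being allocated into either of the two groups". The only thing allocated is acupuncture or sham; no arm or subgroup is given a different number or frequency of sessions.

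Table 1 schedules the NIH-CPSI total score at baseline and at every week from 1 to 8. *Primary outcome measures* adds: "After we have collected data for 8 weeks, the average score from each week will be calculated".

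**The concern.** The GEE sentence asks about dose: does a patient gain more by having more sessions? Answering that needs patients who differ in session number for reasons unrelated to time since start and to prognosis. This design schedules no such difference. As the weeks pass, sessions accumulate at the same rate for everyone, and so does anything else that changes with time: natural course, regression to the mean after entry at a score of 15 or more, and the response to sham.

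What is at stake is how a secondary result is read. A fall in score, or a widening gap between the arms, could be reported as evidence that more sessions give more benefit, when the data show only how scores or differences move over 8 weeks.

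**Working it through.** **Inputs.** Three sessions a week for 8 weeks (abstract; *Treatment group*). Same schedule in sham (*Control group*). Weekly NIH-CPSI totals at weeks 1 to 8 (Table 1). 34 patients per group (*Sample size calculation and statistical analysis*).

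**1. The stated session count.** 3 x 8 = 24, as the article says.

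**2. Sessions against week on schedule.** Let W = 1, ..., 8 be the week and S the cumulative scheduled sessions. Then S = 3W = 3, 6, ..., 24 in both arms. The correlation of S with W is 1.000, and the matrix [1, W, S] has rank 2, not 3. In a model with both effects,

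b0 + bW·W + bS·S = b0 + (bW + 3·bS)·W,

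so only the sum bW + 3·bS can be estimated. No data collected under this schedule can split it.

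**3. Adding the arm.** With A = 1 for acupuncture and 0 for sham, an arm-by-session term is g·A·S = 3g·A·W. This is the linear arm-by-week term rescaled by 3. It shows whether the difference between arms changes with time. It does not show whether sessions cause the change.

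**4. Missed sessions.** The article gives no attendance rate, so a range was assumed, with each session attended independently at random:

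| Assumed attendance | Correlation of attended cumulative sessions with week | Share of session variance not explained by week, 1 - r² |
|---|---|---|
| 95% | 0.993 | about 1.5% |
| 90% | 0.985 | about 3% |
| 80% | 0.967 | about 7% |

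The last column uses the unrounded correlations. Random attendance is the favourable case. Real attendance is not randomised and may depend on response or on a guess about allocation. The *Discussion* itself allows that dropout may be relatively high in the control group.

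**5. What different models would report.** This is an illustration by simulation: 34 per arm, 8 weekly scores, exchangeable GEE, 400 runs per setting. Between-patient SD 5, residual SD 3 and the slopes below are assumptions, not figures from the article.

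| Truth simulated | Term tested at 5% | Share of runs significant |
|---|---|---|
| No session effect; both arms fall 0.5 points a week; attendance 80% to 100% | Sessions, with arm but no interaction | 100% |
| Same | Arm x sessions | 6% to 7% |
| As above, full attendance, and acupuncture benefit grows by 0.4 points a week with elapsed time alone | Arm x sessions | 94% |

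Without an interaction, the session term picks up the shared trend. With it, the shared trend drops out and rejection is close to nominal. The third row shows the remaining limit: the interaction is significant even though only elapsed time was at work.

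**The case against.** The strongest reply is that this is a small clause. It depends on non-normality and on need, appears neither among the listed outcomes nor in Table 2, and may never be run. That is right. A reader might infer that the trial's objective cannot be met, but *Aim* names only the efficacy of acupuncture, and the randomised comparison that addresses it does not depend on session number.

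A second reply is that model terms belong in an analysis plan that is not shown, and that the sham arm's identical schedule is exactly what allows a shared trend to be removed. This also stands. A reader might infer that the analysis is bound to report a false dose effect. The article does not support that, because it does not say that sessions would be fitted without an arm interaction. The reply does not rescue the question itself, though: choosing terms later cannot create variation in session number that the schedule lacks.

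Two further inferences should be resisted:

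- One might divide the changes in the sample-size paragraph by 24 to size a spurious per-session effect. The sham figure there comes from a 10-week course, and 13.3 is called a difference, not a decrease within the acupuncture arm. No reliable per-session figure follows.
- One might fault the *Discussion* for saying that "these scores will indicate the weekly efficacy of acupuncture during the 8 weeks of treatment" on the ground that a single 8-week mean cannot show this. The sentence speaks of scores in the plural and then treats the mean value as something additional, so no error is shown.

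Finally, it can be said that the remedy mostly relabels. For a linear term that is so, but the label decides what the trial may claim.

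**Conclusion.** The point holds as a limited one. On schedule, session number and week are the same variable up to a factor of 3, so whether more sessions give more efficacy cannot be answered. This follows from the fixed regimen alone and needs no assumption. That missed sessions help little rests on the assumed 80% to 95% attendance and on attendance not being randomised. The simulated rejection rates illustrate the mechanism under assumed slopes and SDs; they do not predict this trial's results.

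The consequence is confined to a secondary, conditional analysis and to the wording of its conclusion. It deserves correction because the present wording invites a dose claim that the design cannot support under any choice of model terms.

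**What to change.** In *Sample size calculation and statistical analysis*, replace the clause on cumulative frequency and increasing sessions with a question that the design can answer. For example:

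> *Weekly NIH-CPSI totals at weeks 1 to 8 will be modelled with arm, week and arm-by-week terms to assess whether the acupuncture-sham difference changes over treatment. Between-arm differences will be reported for each week. This analysis describes the time course under a fixed regimen and is not evidence that more sessions give more benefit. Any analysis of attended sessions is exploratory and observational.*

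GEE can remain the method. The cost is a change of wording and a standard repeated-measures analysis of scores already scheduled in Table 1. No visits, data or treatment arrangements change. The trial gives up only a dose claim that it could not have supported.
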